### 2.2. Intervention

Intensive training and support within each intervention community will be oriented around strengthening WHO systems building blocks [24,25] (leadership, workforce development, resources, intelligence) and the New South Wales capacity-building framework [26] (partners and networks) in community settings. This includes mapping existing systems and using these maps to develop and implement whole of systems change with community members and implementation support to optimize interventions. Our pilot work [27] shows that community members were able to identify multiple systems that impact childhood obesity (examples range from improvements in individual health literacy, changes to school food and physical environments, banning of sugar-sweetened beverages within institutions, and local government regulation for better health) and design interventions that consider non-linearity, feedback and complexity.

The system intervention will be implemented by community members (parents and leaders from local government, education, clubs, health agencies, and businesses) with influence on environments in which children experience the key obesity risk factors. Partners will convene new and existing coalitions of community leaders who have the authority, capacity, and networks to lead systems change across the community. These leaders will form a steering group comprising members who are prepared to prioritize changing community systems to healthier food choices, physical activity and childhood obesity prevention across the intervention design process (Table 2). The process is typically conducted within a six-week period with six monthly reviews to capture systems change.

This systems-oriented intervention is similar to previous community capacity-building interventions [28] but builds on them in a number of critical ways. It adds: (1) a new way of thinking about embedding actions in systems; (2) an explicit picture of current community assets in relation to systems; (3) a process for enhancing community engagement in their own systems; (4) a dynamic logic model that adapts to change rather than a fixed linear model; (5) a planning tool for developing and prioritizing a broader set of community-wide actions; (6) a communications device to engage wider stakeholders; (7) a set of tools for community diagnostic and evaluative measurements; (8) an approach that is scalable and sustainable; (9) economic evaluation that utilizes conventional appraisal alongside newer approaches that capture interactions and dynamic changes through time; and, (10) empirical evaluation of the participating community partners’ social networks, and roles that these social networks play in intervention diffusion and increasing community capacity.

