**Figure 2 ijerph-13-01143-f002:**
[figure not shown]
Hypothesis testing over time for the WHO STOPS trial.

**Table 1 ijerph-13-01143-t001:** Study design for the WHO STOPS cluster randomized controlled trial.

Community Type	*n*	Baseline	Step 1		Step 2	
Participant communities	5	**^#^ *** (0)	**^#^** (0)	**^#^ *** (0)	**^#^ (1)**	**^#^ * (2)**
	5	**^#^ *** (0)	**^#^ (1)**	**^#^ * (2)**	**^#^ (3)**	**^#^ * (4)**
External control	13	***** (0)	(0)	***** (0)	(0)	***** (0)
Year		2015	2016	2017	2018	2019

**^#^** Data collection systems mapping; ***** Date collection individual outcomes; (X) = Years in intervention group; Data in bold denotes intervention period.

**Table 2 ijerph-13-01143-t002:** Intervention design activities.

Workshop	Content
**3 h Workshop 1** Problem Identification	Background, evidence, plan presentation; fill in community capacity index; develop system logic model for “causes of childhood obesity in their community” (outcomes evidence translation, baseline measurements, base systems model).
**3 hour Workshop 2** Problem Refinement	Further evidence presentation; fill in social network analysis questionnaires; validation of system logic model on contextualised caused of childhood obesity constructed from the previous workshop (outcomes-further baseline data and knowledge translation and first validation of model).
**Half-day Workshop** Solution Formulation and Prioritisation	Steering group recruits between 50 and 200 champions from across the community who validate the systems logia model and identify priority actions for each sub-system (e.g., water system, school system, food system) related to them (outcomes; wider community validation of model and action plans).
**2 h Workshop 2** Solution Integration	Review the consolidated priority actions (outcomes; translate to institutional action plans).
**1–2 h Evaluation****Sessions** Adaptive Solutions	Steering: six monthly sessions to identify subsystem changes and modifications to the systems map (outcomes such as individual child measures, process change; follow up system measures).

**Table 3 ijerph-13-01143-t003:** Primary and secondary outcomes of interests and proposed instruments.

Item	Outcome(s) of Interest	Instrument/Measure
Anthropometry	Body Mass Index-z score	Height and weight
	Overweight and obesity prevalence [37,38]	

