Physical activity and sedentary behavior	Minutes per day (min·d^−1^) spent in moderate-to-vigorous physical activity and sedentary behavior	Modified Core Indicators and Measures of Youth Health [39] and School Health Action, Planning and Evaluation System [40] Accelerometer (sub sample)
	Proportion of participants meeting the national physical activity guidelines and screen-time recommendations [41]	
Diet Type, frequency	Usual serves of: fruit and vegetable daily	Modified version of the Simple Dietary Questionnaire [42]
	Usual frequency of non-core foods (e.g., take-away food, chips, lollies, chocolate)	
	Usual frequency of sugar-sweetened beverages	
	Proportion of participants meeting the Australian Dietary guidelines for fruit and vegetable intakes [43]	
Quality of life	Global summary score	Paediatric Quality of Life Inventory 4.0 (PedsQL)^TM^ [44] CHU-9D Child Health Utility Index [45]
	Physiological health summary score	
	Physical health summary score	
	Child Health Utility Index (CHU-9D )	
Environments	School healthy eating and activity policies and practices	Modified version of the Be Active Eat Well Environment audit [38], the International study of childhood obesity, lifestyle and the environment tool [46]
	Adherence to physical education and sport education mandate for Victorian primary schools	
Social networks (ecological data)	Characteristics of Community Leader social networks	Validated measures of socio-centric and ego-centric communication and collaboration networks
	Density, diffusion, change dynamics, key players	

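### The leader-network questionnaire labelled as baseline is scheduled at Workshop 2, after leaders have been convened and have worked together, so early network change may be missed unless the 2015 systems data collection already covers it

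*Protocol article*

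**What the plan says.** **Networks as a target.** Section 2.2 (Intervention) says that training and support are built around WHO systems building blocks and "the New South Wales capacity-building framework [26] (partners and networks) in community settings".

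**Convening.** The same section says: "Partners will convene new and existing coalitions of community leaders who have the authority, capacity, and networks to lead systems change across the community". The steering group is then formed from them. On duration it says: "The process is typically conducted within a six-week period with six monthly reviews to capture systems change".

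**Order of the workshops (Table 2).** Workshop 1 includes "fill in community capacity index; develop system logic model for “causes of childhood obesity in their community". Workshop 2 lists "Further evidence presentation; fill in social network analysis questionnaires", together with validation of the model built in the previous workshop. Its outcomes are given as "outcomes-further baseline data and knowledge translation and first validation of model".

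**Use of the network data.** Table 3 lists "Characteristics of Community Leader social networks" as an outcome of interest, with density, diffusion, change dynamics and key players. Section 3 (Analysis Plan) intends longitudinal network models of how networks change and of what predicts new relationships.

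**Other systems data collection.** Table 1 marks systems-mapping data collection in all ten communities at the 2015 baseline, at zero years in intervention. In the five later-start communities it is marked again in 2016 and 2017, still at zero years. The article does not say whether the network questionnaire is part of that collection.

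**The concern.** A baseline for a change analysis should precede the exposure whose effect is studied. Here the first components of the intervention bring leaders together, partly in new coalitions, and have them build a model jointly. Those steps can create the communication and collaboration ties that the questionnaire measures. A tie formed during convening or at Workshop 1 and reported at Workshop 2 would enter the first wave as an existing tie. It could not then appear as a new one.

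At stake is the evidence on the first objective in the Abstract, strengthening community action. Section 2.2 also counts evaluation of partners' social networks, and of their role in building community capacity, among the ways this intervention goes beyond earlier ones. Once leaders have been convened, the untouched network can be recovered only by recall, so the order has to be settled beforehand.

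**Working it through.** The article gives no figure for network size, density or change, so there is no stated result to reproduce. The check is a comparison of passages, followed by an illustration with assumed values.

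**Step 1: sequence from the article**

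| Order | Event | Source |
|---|---|---|
| 1 | Systems data collection in all ten communities, 2015, zero years in intervention; content regarding networks not stated | Table 1 |
| 2 | New and existing coalitions convened; steering group formed | Section 2.2 |
| 3 | Workshop 1: evidence and plan presented, systems model developed jointly | Table 2 |
| 4 | Workshop 2: network questionnaire filled in, output labelled further baseline data | Table 2 |
| 5 | Half-day workshop with 50 to 200 champions, then solution integration | Table 2 |
| 6 | Six-monthly sessions | Section 2.2, Table 2 |

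Table 2 is the only place where the article gives a time for the network questionnaire. That time follows events 2 and 3, which are parts of the intervention.

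**Step 2: which ties are affected.** Only ties formed during events 2 and 3, early in a process of about six weeks, are absorbed into the first wave. Ties formed during events 5 and 6 still count as change.

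**Step 3: effect on density.** Let d0 be density before convening, d1 density at follow-up, and f the share of the net gain already present at Workshop 2. Assume a fixed membership and that early ties persist. Then:

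- density at Workshop 2 = d0 + f × (d1 − d0)
- measured change = d1 − [d0 + f × (d1 − d0)] = (1 − f) × (d1 − d0)

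With assumed d0 = 0.10 and d1 = 0.20, the true change is 0.10:

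| f | Measured change |
|---|---|
| 0 | 1.00 × 0.10 = 0.10 |
| 0.10 | 0.90 × 0.10 = 0.09 |
| 0.25 | 0.75 × 0.10 = 0.075 |
| 0.50 | 0.50 × 0.10 = 0.05 |

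The densities and f are assumptions. The shortfall is zero if no ties form before Workshop 2 and grows in proportion to f.

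**Step 4: other measures.** The formula does not carry over to centrality, opinion-leader or key-player measures, which depend on who gains ties and not only on how many. It also fails if membership changes between waves. In those cases the direction of any bias is undetermined.

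**The case against.** The strongest reply is Table 1. It schedules systems data collection in every community in 2015, and the Analysis Plan moves from network analysis to what it calls additional systems measurement, as if network analysis were one such measurement. A network wave before the intervention may therefore exist, and an article may leave the instrument-by-wave schedule to the full protocol. This stands as a condition on the finding. It does not remove it, because Table 2 still attaches a baseline label to a questionnaire filled in after exposure has begun. If there is a 2015 network wave, the article leaves unclear which wave is the baseline.

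A second reply is that attending one three-hour workshop is not in itself a communication or collaboration tie, that some coalitions already existed, and that a look-back question could largely remove the effect. This also stands. The article gives neither a tie definition nor a recall window, so the size cannot be judged.

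A reader might infer more than the article supports:

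- **That network change is definitely understated.** This needs ties to form early and persist, and it applies to density and tie counts only.
- **That the early weeks could absorb the whole gain or more.** This would require as many net ties from convening and one workshop as from the entire follow-up, or a net loss afterwards. Nothing in the article points to that.
- **That the community capacity index has the same fault, because Table 2 names it after the presentations in Workshop 1.** This treats a summary cell as a strict running order, which it need not be.

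**Conclusion.** The point holds conditionally. On the only timing the article gives, the network measure labelled baseline is taken after leaders have been convened and have worked together in Workshop 1. Unless the 2015 collection in Table 1 includes the questionnaire, the first network wave is an early post-exposure wave. Change in density and tie formation may then be understated by a factor (1 − f), with f unknown. This rests on early ties forming and persisting, a stable membership, and questions that do not look back to the time before convening.

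The consequence is confined to the network outcomes. The primary outcomes, the randomised comparison of BMI-z and the sample size do not depend on this questionnaire. The correction is worth making because it is cheap and because a missed pre-convening network is hard to recover later.

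**What to change.** 1. State whether the 2015 systems data collection in Table 1 includes the leader-network questionnaire. If it does, name that wave as the baseline in the longitudinal network models.
2. If it does not, send the existing questionnaire with the invitation, before leaders first meet, and use that wave as the baseline. Completion on arrival at Workshop 1, before any group activity, is second best, because convening has already happened.
3. If the questionnaire is also kept at Workshop 2, describe and analyse it as an early post-exposure wave and remove the baseline label in Table 2.

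**Cost.** One existing form moves earlier by days to weeks, with no new instrument. Leaders who join later need the form when they join, and response to a mailed form may be somewhat lower. Under Table 1 five communities start two years after the others, so the revised order could be used there even if the first five had already begun.

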### 2.3. Characterizing and Intervening in Systems

Using Action Research [29] and Knowledge Translation and Exchange frameworks [30], the nature of the intervention is allowed to iterate and develop over time. The following measures will be taken and be fed back to progressive design and implementation support workshops described above.

#### Systems Maps

Group model building (GMB) will be used to develop causal maps (causal loop diagrams) as qualitative representations of the feedback mechanisms and delays of systems driving obesity trends within each community. GMB is a participatory systems science method for engaging stakeholders in the process of developing informal maps and formal models with computer simulation [31]. Central to GMB is the explicit design and facilitation of a sequence of boundary objects that allow all diverse stakeholders to describe dependencies between different elements of systems [32,33,34].

The GMB workshops comprise facilitated activities that provide the skills and techniques necessary for participants to develop system maps using GMB scripts [35,36]. In each community, an evidence-based, community-specific systems logic model will be co-developed and validated by participants and researchers and priority actions formed. Subsequent workshops (six monthly) will identify subsystems changes and modifications to systems. Quantitative data will be collected to describe key variables in the system logic model. Where data are not available, community measures of variable strength and change will be collected. These data will be used for the economic analysis to describe the level and cost of intervention activity in relation to the measured outcome.

### 2.4. Evaluation

#### 2.4.1. External Control Communities

Thirteen additional Victorian communities were selected in the 2014/2015 financial year as comparison (i.e., no intervention) sites [37]. Baseline data was collected in parallel to the baseline for this study from 2561 of 2959 eligible students in Victorian primary schools (response rate = 87%). The outcome measures used were identical to those in the current proposal, collected under an opt-out consent model, and in regions geographically dispersed from the GSCRV. Measures will be repeated in 2016/2017 and 2018/2019 to provide a detailed picture of changes in BMI-z (Body Mass Index z score) and risk factor prevalence outside the GSCRV. This will also provide for some assessment of contamination across areas. We will be able to assess regional differences though not broader efforts. For example, we will be able to assess the effect of different localized health promotion media, though not state-wide or federal coverage.

#### 2.4.2. Primary and Secondary Outcomes

Primary outcome: change in childhood BMI-z and obesity prevalence. Secondary outcomes: change in children’s diet and physical activity (PA) behaviours, community systems, and settings environments for food and PA. The previously published detailed methodology of the sustainable monitoring system is briefly outlined below [17,37].

#### 2.4.3. Anthropometry and Behaviours

Participants will be all children in grades two (7–8 y), four (9–10 y) and six (11–12 y) available on the day of data collection at their school who have not returned an opt-out consent form. All primary schools in the GSCRV will be invited to participate using the approach outlined below.

### 2.5. Measures/Instruments

All eligible children (grades two, four and six) in consenting schools will have height and weight measured by trained personnel. Children in grades four and six will be invited to complete, on an electronic tablet (i.e., iPad), survey instruments (Table 3) selected for suitability, reliability and validity for these age groups [17].

### 2.6. Procedures

In Term 1 of each study year (2015 baseline, 2017 and 2019) presentations will be made to school principal networks (agreed partners), with written invitations and an information pack sent to each school principal, followed up with phone calls and/or personal visits to recruit schools. Assembly and classroom presentations will be made to all children in the target grades regarding the study, at which time the Plain Language Statement and opt-out consent form will be distributed. All children in each target grade will be enrolled unless they return an opt-out consent form signed by their parents/guardians or opt out verbally. Measurements will typically be conducted over a one-day visit to each school in the second term of each year (March to June). A team of up to six trained data collectors (all with current Working with Children Checks or equivalent) will collect anthropometric and survey data in one class period. Data collectors will be trained by study leads in anthropometric measurement, accelerometer fitting, questionnaire delivery and sensitivity when engaging young children.

### 2.7. Sample Size

Based on school enrolment data, we estimate that there are 5050 children in the GSCRV in grades two, four or six across 84 primary schools in the region. Using an opt-out consent process, which delivers a >90% response rate, and assuming that 75% of schools will participate, we expect to measure more than 3000 children at each study wave meaning 3000 observations at each step and 9000 across the three study data points. BMI-z standard deviation (1.2) and intra-cluster correlation (0.027) were estimated in a previous study of >2500 Victorian school children (2014–2015). Under the stepped wedge design (ten clusters, three data collection points, five clusters) randomized to intervention at step 1, there will be an average of 300 children in each cluster, and the minimum detectable difference in BMI-z between groups with 80% power will be 0.13. This compares favourably with the observed difference achieved in previous successful intervention studies in children of 0.18, which was associated with a 3% reduction in prevalence of overweight and obesity over three years [7,8,9].

While the power for the current study is based on the stepped wedge design alone, the external parallel control group of 13 communities will add an additional comparative power to this trial.

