## 2. Methods

This is a cluster randomized stepped wedge trial (two steps) in ten communities. The unit of randomisation and intervention is the community (rather than individual children). Following baseline measurement of all eligible children in all ten communities (2015), five communities will be randomized to the intervention in year one (step one) and the remaining five will be entered into the intervention two years later (step two) (Table 1). Grades two, four and six children in all clusters will be measured in the baseline year (2015), year two (2017) and year four (2019). Data collection every second year reflects a more cost-effective measurement approach and a realistic timeframe to begin to see changes in weight status among intervention populations. Opportunities and funding for longer-term data collection (i.e., a five- and ten-year follow up) will be actively sought in due course.

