## 3. Analysis Plan

Social network analysis (SNA) [47] will be used to quantify the strength and importance of relationships among people and organizations who have control over environments that affect children’s health [48]. Social network analysis software (e.g., “SNA” and “network” in R [49] will be used to calculate network statistics for each community including density and centrality and “opinion leader” positions, which are statistics used to identify people in the network who send or receive the most connections to others (the former indicating influence, the latter prominence), or who occupy other central or bridging positions in a network that are important to network diffusion and connecting relatively disconnected areas of the network. Social network dynamics will be modeled using longitudinal network models to determine how the networks change over time, the factors that predict the formation and maintenance of new relationships, and the role of the network in the diffusion information, knowledge and practice. Additional systems measurement will comprise evaluation of change in systems maps, tracking of change in subsystems and process evaluation of the communities’ responses to the systems intervention. The grounded logic models developed through this process will also allow the addition of other data sources, whether bespoke or routine data, for an understanding of the change in systems.

The effect of the intervention on the main outcome (BMI-z) will be assessed using a linear mixed model with cluster as a random effect (community) and time (step), intervention and interaction of time by intervention as fixed effects. Because intervention enrolment will be staggered, data will be analyzed following two different approaches: (1) an intention to treat principle irrespective of when the enrolment effectively occurred; and (2) considering actual enrolment time. Secondary outcomes will be analyzed by fitting a generalized linear mixed model with link and distribution selected according to the variable (Figure 2). Missing outcomes (which we anticipate will be sparse due to the selection criteria “child present at school on the day of data collection”) will be managed using an inverse probability weighting approach.

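### Many children are measured at more than one wave, but the sample size and the primary model treat each wave as a separate sample of children, so the planned standard error does not match the design

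*Protocol article*

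**What the plan says.** Section 2 (Methods) fixes the schedule: "Grades two, four and six children in all clusters will be measured in the baseline year (2015), year two (2017) and year four (2019". Section 2.4.3 defines the participants at each wave as all children in these grades "available on the day of data collection at their school who have not returned an opt-out consent form", and section 2.6 has schools invited and children enrolled afresh in each study year. Section 2.7 counts "3000 observations at each step and 9000 across the three study data points", takes one SD and one ICC ("BMI-z standard deviation (1.2) and intra-cluster correlation (0.027) were estimated in a previous study"), and concludes that "the minimum detectable difference in BMI-z between groups with 80% power will be 0.13". Section 3 gives the primary analysis as a "linear mixed model with cluster as a random effect (community) and time (step), intervention and interaction of time by intervention as fixed effects". The article does not say that children recur across waves or whether their records are linked.

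**The concern.** Grade two in 2015 is grade four in 2017 and grade six in 2019; grade four in 2015 is grade six in 2017; grade two in 2017 is grade four in 2019. The same children therefore supply many of the observations, and a child's BMI-z is strongly correlated over two years. A model with only a community effect treats those repeat measurements as independent given community. Two things are at stake. First, the reported standard error does not describe the real sampling variation of the estimate, so the test does not run at its nominal level. Second, within-child change, which is an informative comparison in this design, goes unused in a trial of ten communities.

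**Working it through.** **Inputs from section 2.7.** Ten communities, three waves, five communities starting at each step, 300 children per community and wave, SD 1.2, ICC 0.027, 80% power, detectable difference 0.13. The significance level and sidedness are not stated.

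**Assumptions, not in the article.** Correlation ρ of a child's BMI-z between waves, 0.7 to 0.85. Share r of grade-eligible children re-measured at the next wave and linked, 0.6 to 0.8. Community effects either stable or with between-wave autocorrelation 0.95 or 0.9. A constant intervention effect, as the single detectable difference implies.

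**1. Overlap.** Each wave has three grade cohorts of about 1000 children. Two of the three were eligible at the previous wave, and one of the three in 2019 was eligible throughout. Five cohorts are involved in all, so with full retention the 9000 observations come from 5 × 1000 = 5000 children. With 75% re-measured, 2 × 2000 × 0.75 = 3000 observations are repeats, leaving 6000 distinct children.

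**2. Reproducing 0.13.** Between-community variance τ² = 1.44 × 0.027 = 0.03888. Variance of a community-wave mean within community e = 1.44 × 0.973 / 300 = 0.00467. The arms differ in exposure only in 2017, so the estimate is d₂ − b(d₁ + d₃), where d is the arm difference at each wave and b = τ²/(2τ² + e) = 0.472. With waves as separate children:

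Variance = (1/5 + 1/5) × [τ² + e − 2bτ²] = 0.4 × 0.006873, so SE = 0.0524.

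One-sided 5%: (1.645 + 0.842) × 0.0524 = 0.130, which reproduces the article. Two-sided 5%: 2.802 × 0.0524 = 0.147. The stated figure thus comes from treating the waves as independent samples of children. Sidedness is a separate question.

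**3. True SE of the planned estimate under overlap.** Shared children add eρ(2/3)r to the covariance of adjacent wave means and eρ(1/3)r² to that of 2015 and 2019. The bracket becomes

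0.006873 − eρ[(8/3)br − (2/3)b²r²].

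At r = 0.75 and ρ = 0.8: 0.006873 − 0.003736 × 0.860 = 0.003660, so SE = √(0.4 × 0.003660) = 0.0383. The model still reports about 0.052 (mean 0.0523 in 1500 simulated trials). Approximate size of the two-sided 5% test: 2Φ(−1.96 × 0.0524/0.0383) = 0.7%; simulated, 1.2%. Over the assumed ranges the formula gives 0.4% to 1.6%. The simulations, at 75% re-measured and ρ from 0.7 to 0.9, gave 0.5% to 1.5%.

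**4. Gain from modelling the child.** Generalised least squares with the child covariance, and a community-by-wave component where there is drift, over r = 0.6 to 0.8 and ρ = 0.7 to 0.85:

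| Community effects | True SE, planned estimate | True two-sided detectable difference | With child effect modelled |
|---|---|---|---|
| Stable | 0.036-0.043 | 0.10-0.12 | 0.07-0.10 |
| Autocorrelation 0.95 | 0.049-0.054 | 0.14-0.15 | 0.12-0.14 |
| Autocorrelation 0.9 | 0.060-0.064 | 0.17-0.18 | 0.15-0.17 |

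If the same children are re-measured at every wave (r in place of r² above), the low end of the first row becomes 0.037; nothing else of substance changes.

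**5. Why a child intercept alone is not enough.** At r = 0.75, ρ = 0.8 and autocorrelation 0.9, a model with community and child intercepts only would report SE 0.028 when the true SE is 0.056, a size of about 33% with variance components held at those values. Approximations that let the misspecified fit re-estimate them give about 12% to 31% for autocorrelation 0.95 to 0.9.

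**The case against.** Four points can be made for the plan.

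- *Repeated cross-sections of all children in fixed grades are a legitimate way to monitor communities, and linkage is the kind of detail an article leaves to the full protocol or analysis plan.* The first half stands. The second does not answer the point: the article writes out the primary model with a single random effect, and that model does not fit its own measurement schedule.
- *The count of 9000 is right.* This stands. A reader might infer that 9000 children were wrongly claimed, but section 2.7 counts observations, and 3 × 3000 is correct.
- *Nothing here produces false positives.* This stands for overlap. A reader might infer that ignoring repeat measures makes the SE too small, as it often does elsewhere. Here the estimate sets 2017 against the other waves within community, so shared children cancel and the SE is too large. With autocorrelation 0.9 the planned test is too liberal (about 10% to 11% in simulation at 75% re-measured), but the cause is the missing community-by-time term: without any overlap the figure is 15%.
- *The size of the gain rests on quantities the article does not give.* This also stands. The upper end of the linkage range may be optimistic. Section 1.1 reports 48 schools in 2015, and 75% of 84 is 63; with equal-sized schools, at most 48/63 = 76% of repeat-eligible children in 2017 attended a school measured in 2015, or about 69% after a 90% response. The 69% school participation in the abstract would allow more.

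**Conclusion.** The concern holds in a limited form. That children recur, and that neither the sample size nor the stated model allows for it, follows from the article without any outside assumption. The consequence with stable community effects is a conservative test and lost precision: reported SE 0.052 against a true 0.036 to 0.043, and actual size about 0.5% to 2%. The gain from modelling the child must be measured from the planned estimate's true precision under overlap. It is tempting to set the linked-analysis figures against 0.147, but that value assumes no overlap at all and so overstates the gain. The fair comparison is 0.10-0.12 against 0.07-0.10 with stable communities, and 0.17-0.18 against 0.15-0.17 at autocorrelation 0.9. These figures depend on the assumed child correlation, linkage and community stability. The overlap does not by itself make the stated 0.13 optimistic. The change should be made, but the trial's validity does not hang on overlap alone.

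**What to change.** - In sections 2 and 2.7, describe the design as an open cohort with overlapping children. Keep the 9000 observations, and add that they come from about 5000 distinct children (full retention) to 6000 (75% re-measured).
- State whether children will be linked across waves. Link them where identifiers and consent allow.
- If linked, fit the primary model with a child random intercept and a community-by-wave random effect, using a small-sample correction for ten communities. Do not add the child intercept without the community-by-wave term.
- If linkage is not possible, use cluster-level or robust inference with a small-sample correction, so that the SE reflects the overlap, and say that waves are analysed as repeated cross-sections.
- Restate the detectable difference under the chosen model, with the assumed child correlation, linked share and community autocorrelation shown as ranges.

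The cost is the matching work and a check that ethics approval and consent cover linkage. Linkage will be incomplete because schools are recruited again at each wave, and the gain is confined to the later waves if the 2015 records hold no identifier.
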